### Study period III (double-blind down-titration period)

Study period III is a 1-week double-blind down-titration period (visits 9–10) from study medication, active drug or placebo. Any patient who completes study period II (visit 9) will continue into study period III. In a blinded fashion, their dose of study medication will be titrated down depending on their final dose in study period II. Placebo-treated patients from study period II will continue placebo treatment in study period III. In order to maintain the blind, all patients will receive the respective amounts (e.g. number of tablets) of study drug (active or placebo). The final visit of this period will be visit 10. See the SOE for the timing of events and the measures to be assessed (Table 1).

### Study population

Overall, *N* = 100 patients (*N* = 50 participants with OCD and *N* = 50 participants with ASD), male or female, with inpatient or outpatient status, aged 6 years (ASD patients)/8 years (OCD patients) to 17 years and 9 months at inclusion, will be randomised into study period II. These patients will be recruited from four centres, i.e. per site approx. *N* ≥24 children and adolescents (*N* = 12–13 with OCD; 12–13 with ASD).

### Inclusion criteria

General inclusion criteria for both patient groups (OCD and ASD):Male or female patientsInpatient or outpatient statusAged 6 years (ASD patients)/8 years (OCD patients) to 17 years 9 months at initial inclusionIQ ≥70 (based on Wechsler scales, four subtests)Clinical Global Impressions-Severity (CGI-S; [53, 54]) score ≥4 (moderately ill; anchored to respective disorder) at BL (visit 3)Ability to speak and comprehend the native language of the country in which the assessments take placeSigned informed consent by parents or legal representativesSigned informed assent by patients (indicating that the subject is aware of the investigational nature and the core aspects of the study and the study is run in accordance with the International Conference on Harmonisation of Technical Requirements for Registration of Pharmaceuticals for Human Use (ICH) Good Clinical Practice (GCP) guideline E6 (1996)Female subject must not have a positive beta-HCG pregnancy test at screening, and must have a negative urine pregnancy test at BL, and agree to comply with applicable contraceptive requirements

Inclusion criteria for subjects with OCD (GOAT-1):*Diagnostic and Statistical Manual, 5th edition* (DSM-5) diagnosis of OCD [2], according to a structured interview (e.g. DISC; [55])

Inclusion criteria for subjects with ASD (GOAT-2):DSM-5 diagnosis of ASD [2], according to the Autism Diagnostic Interview-Revised (ADI-R; [56])

### Exclusion criteria

General exclusion criteria for all subject groups:Intellectual disability (IQ <70)Body weight below 20 kg at BLMajor physical illness of the cardiovascular, endocrine, pulmonary, or the gastrointestinal systemContra-indications for memantine, according to the Summary of Product Characteristics (SPC)History of or present clinically relevant somatic acute or chronic disorder that, in the opinion of the investigator, might confound the results of tolerability/safety assessment, or prohibit the patients from completing the study, or would not be in the best interest of the patientSubject has failed to respond, based on investigator judgment, to an earlier adequate course (dose and duration) of the investigational drug therapy, memantineSubject has a documented allergy, hypersensitivity, or intolerance to, memantineSubject has a positive urine drug screen result at screening or BL (apart from earlier prescribed medication; retest and negative result at BL needed then)Subject has taken another investigational product or taken part in a clinical study with 30 days prior to screeningSubject is female and is pregnant or lactatingFor those subjects intending to participate in the neuroimaging assessments: all contra indications for MRI assessment, such as the presence of metal objects in or around the body (e.g. pacemaker, dental braces)Patients/parents will not be excluded from the study if they do not agree to participate in certain sets of assessments (e.g. neuroimaging, blood sampling for bioanalytical analyses)

### Randomisation

Randomisation will be done in a 1:1 ratio (active drug: placebo).

### Sample size calculation

The total sample size of approx. *N* = 100 paediatric patients (*N* = 50 in each diagnostic subgroup (OCD, ASD)) across trials will not allow for confirmatory statistical analyses but will be adequate for descriptive statistics, for pilot-testing of the chosen glutamatergic medication (memantine), and for hypothesis generation.

### Endpoints

The endpoint for primary objective 1 (clinical effectiveness) is the baseline-to-endpoint change of compulsivity as measured by the CY-BOCS total score (all patients). The endpoints for primary objective 2 (tolerability and safety) are adverse event (AE) rates, derived from both spontaneous reporting and a structured AE instrument, the (adapted) Pediatric Adverse Event Rating Scale (PAERS; [57]).

The endpoints for the secondary objectives (other effects) are additional clinical outcomes, e.g. response rates, response defined as at least 30 % reduction versus BL on the primary outcome scale (CY-BOCS total score, for OCD, ASD patients) plus Clinical Global Impressions-Improvement (CGI-I; [53, 54]) score of 1 (very much improved) or 2 (much improved); baseline-to-endpoint changes in the total score of the Aberrant Behaviour Checklist-Community (ABC-C; [58–60]: ASD patients).

For the tertiary objective (genetic pathways) genotypes of single common and rare variants in candidate genes, and also combined genetic variants in whole genes or neurotransmitter systems/gene pathways will be investigated and further laboratory assessments of various proteins in blood plasma will be performed. Neuroimaging data will be analysed according to the TACTICS COMPULS protocol (see below) in order to explore the effects of glutamatergic interventions at the level of the structure, function and biochemistry of the fronto-striatal circuits.

### Measures

#### Diagnostic instruments

##### Diagnostic Interview for Children (DISC)

In order to determine diagnoses of OCD, e.g. the Diagnostic Interview for Children (DISC; [55]) will be used and administered by trained investigators. In order to assess most common co-morbidities, the modules for tic disorder, oppositional-defiant disorder, and conduct disorder will be applied, additionally; this interview will be completed with parents of patients in all groups.

##### Autism Diagnostic Interview-Revised (ADI-R)

The Autism Diagnostic Interview-Revised (ADI-R; [56]: adapted short version, focusing on criteria relevant for diagnosis) will be administered by a certified interviewer to determine the ASD diagnosis. This interview covers the core domains of ASD.

##### Clinical change

Rigid and compulsive patterns of behaviour will be measured in all participants, thus both patient groups, using the following measures:*Aberrant Behaviour Checklist-Community (ABC-C)*The Aberrant Behaviour Checklist-Community (ABC-C; [58, 59]) is a parent-rated 58-item scale assessing behaviour and psychiatric symptoms across the five domains: Irritability, Agitation and Crying, Lethargy/Social withdrawal, Stereotypic behaviour, Hyperactivity/Noncompliance and Inappropriate speech.*Children’s Yale-Brown Obsessive-Compulsive Scale (CY-BOCS)*The Children’s Yale-Brown Obsessive-Compulsive Scale (CY-BOCS; [52]) is a clinician-rated 10-item scale, with each item rated on a 5-point scale from 0 = ‘no symptoms’ to 4 = ‘extreme symptoms’, with, apart from a total score, subtotals for obsessions (items 1–5) and compulsions (items 6–10).*Children’s Social Behaviour Questionnaire (CSBQ)*The Children’s Social Behaviour Questionnaire (CSBQ; [61–63]) is a 49-item parent-rated questionnaire that aims to quantify the different behavioural dimensions along which children with ASD vary. In this study we will use the total score and rigidity(-related) subscale scores (e.g. Stereotyped behaviour, and Fear of and resistance to changes).*Repetitive Behaviour Scale-Revised (RBS-R)*The Repetitive Behaviour Scale-Revised (RBS-R; [64]) is a 43-item parent-rated questionnaire for measuring the presence and severity of a variety of forms of restricted, repetitive behaviour. It consists of six subscales: Stereotyped behaviour, Self-injurious behaviour, Compulsive behaviour, Routine behaviour, Sameness behaviour, and Restricted behaviour.*Clinical Global Impression-Severity (CGI-S)*The Clinical Global Impressions-Severity (CGI-S; [53, 54]) is a single-item rating of the clinician’s assessment of the severity of symptoms in relation to the clinician’s total experience with OCD or ASD patients. Severity is rated on a 7-point scale (1 = normal, not at all ill; 7 = among the most extremely ill subjects).*Clinical Global Impression-Improvement (CGI-I)*The Clinical Global Impressions-Improvement (CGI-I) [53, 54] is a single-item clinician rating of the total improvement (or worsening) of the patient’s symptoms since the beginning of treatment regardless of whether the improvement (or worsening) was thought to be due entirely to the drug treatment. Improvement/worsening is rated on a 7-point scale (1 = very much improved; 7 = very much worsened).*Children’s Global Assessment (C-GAS)*The Children’s Global Assessment Scale (C-GAS; [65]) is a global, unidimensional clinician rating of social and psychiatric functioning in children aged 4–16 years. Scores on the measure range from 1 (most impaired) to 100 (healthiest).

#### Additional measures

##### The Child Behaviour Checklist (CBCL, 6–18)

The Child Behaviour Checklist (CBCL, 6–18; [66] cf. [67]) will be applied – parent-reported – at BL in order to assess general symptomatology (cf. SOE). It is a standard instrument that allows evaluating various behavioural domains in children and adolescents; it has been psychometrically validated and is available in the very country languages involved in this study. In this study, the ‘problem behaviour’ section will be applied only, not the ‘competencies’ part. It may also allow for analyses on mediating factors for primary and secondary outcome parameters.

#### Health outcomes/Quality of life measures

##### Child Health and Illness Profile (CHIP-CE)

The Child Health and Illness Profile (CHIP-CE) Parent Report Form [68] has been used in a number of paediatric trials with psychotropic medications and allows comparisons with findings from paediatric populations with non-psychiatric disorders. It is available in the respective country languages involved in this study.

#### Safety evaluations

##### Spontaneous adverse event reporting

Spontaneous adverse event reporting will be based on standard questioning of patients and parents by the investigator at each visit.

##### Pediatric Adverse Event Rating Scale (PAERS)

In a second step, the structured Pediatric Adverse Event Rating Scale (PAERS; [57]: adapted/shortened version) will be applied at each visit, beyond standard AE reporting solicited by open questioning, in order to systematically collect AEs; the investigator-rated version will be used, based on parent- and patient-information.

Only PAERS reports on ‘serious’ AEs will be added to the ‘spontaneous reporting of AE results’ and be reported immediately.

### Laboratory tests

Blood and urine samples will be collected at the times specified in the study SOE (Table 1) and when clinically indicated. Standard laboratory tests including clinical chemistry, electrolytes, urine analysis, and haematology panels will be performed. Laboratory tests will be analysed by a local laboratory, at each study site. Urine drug screening will be performed at study start and in case of suspected intoxication, overdose, etc., at the discretion of the investigator, at regular or unscheduled visits. If agreed to by patients and parents, 30 ml blood will be drawn from participants for biobanking purposes, for DNA isolation, and assessment of biomarkers for which either serum or plasma samples are prepared. The venipuncture will be performed by medical staff, e.g. a trained nurse practitioner, who has considerable experience of working with children.

### Molecular-genetic material

Genome-wide genotyping of common and more rare variants will be performed using PsychChip (or similar) (https://sites.google.com/a/broadinstitute.org/psych-chip-resources/home). The resulting data will be analysed in two ways: (1) the variation in the genes will be analysed for rare variants that appear to have deleterious effect on gene function (based on conservation, predicted changes in gene-product structure and function). Those will be studied further by protein studies; and (2) in addition to this, gene-wide burden analyses [69] of rare as well as common variants will be performed to identify an association with treatment response or diagnosis. All analyses will be corrected for multiple testing as appropriate.

### Other biological material

Protein levels of blood-expressed compulsivity and addiction genes will be monitored using multiplex immunoassay profiling of peripheral blood cells and serum. This work will be performed in close collaboration with the laboratory of Professor [name] in Cambridge/UK. In addition, at the Nijmegen centre there are expertise and facilities for High Pressure Liquid Chromatography (HPLC) in blood platelets (for products of neurotransmitter pathway genes). Earlier work has shown that potential compulsivity- and addiction-relevant molecules such as hormones, cytokines and neurotransmitters such as glutamate and serotonin, are measurable in serum and blood cells.

### Neuropsychological assessment

All neuropsychological tasks performed within this study are suitable for subjects from the age of 5 years to adulthood.

#### Neurocognitive assessment battery

In order to explore potential medication effects (improvements, impairments) to cognitive functioning, a neurocognitive assessment battery, the Amsterdam Neuropsychological Test Battery (ANT), will also be used, including attentional, set-shifting, motor speed and inhibition, cognitive flexibility, and verbal working memory tasks.

#### Wechsler Intelligence Scale for Children (WISC-III)

The WISC-III will be performed in order to determine the general IQ level of the patient if not done within 2 years from BL [70]. Patients must have an IQ of >70 (based on, at least four subtests, two verbal plus two performance tests) from the Wechsler IQ Scales, e.g. WISC, WAIS. In this study four subtests will be used, e.g. Vocabulary, Similarities, Block Design, and Matrix reasoning [71]. Age- and country-specific adaptations may be used.

### Neuroimaging

If agreed to by patients and parents, neuroimaging of the patients will be performed by MRI according to the protocol of another TACTICS project, COMPULS. The aim of COMPULS is to identify neural, neurocognitive, genetic, and biomarker mechanisms underlying compulsive behaviours in high-risk subjects and controls. The primary objectives are to examine whether (1) structural and functional abnormalities of the fronto-striatal circuits are related to the development of compulsive and impulsive behaviour in ASD and OCD, and (2) the glutamate system is a key modulator in these fronto-striatal circuits. The COMPULS study has a mixed cross-sectional longitudinal design with assessments at two time points. Measurements are: MRI (structural MRI, functional MRI, resting state MRI, Diffusion Tensor Imaging (DTI)), MRS (spectroscopy), plus multiple tasks reflecting cognition and behaviour (cf. website: http://www.tactics-project.eu; WP04).

### Vital signs

Vital signs including body temperature, heart rate (pulse), and blood pressure will be recorded as specified in the study SOE (Table 1).

### Height and weight

Height and weight will be recorded as specified in the study SOE (Table 1); measurements will be performed according to standardised procedures across study sites.

### Electrocardiogram (ECG)

ECGs will be performed following standard procedures at the visits outlined in the SOE (Table 1).

### Medication and dosing

The investigator or his/her designee is responsible for explaining the correct use of the investigational agent(s) to the patients and parents, verifying that instructions are followed properly, maintaining accurate records of study drug dispensing and collection, and of returning all unused medication at the end of the study.

This study involves a comparison of an active drug (memantine) with matching placebo. During study period II, medication will be initiated and modified according to the weight group of the patient at BL (visit 3). Dosing may then be increased (or decreased) by 5 mg/day increments, respectively, at specified visits/dates according to the weight of the subject (cf. Table 2). Stepwise up-titration is recommended to the target dose or the highest tolerable dose by week 4, accordingly. Dosing should remain stable during the last 4 weeks of study period II unless a dose reduction is necessary for tolerability or safety reasons. In case of dose-adjustments due to AEs unscheduled visits can be performed (for stepwise down-titration). Patients who cannot tolerate the minimum daily dose specified (5 mg/day) will be discontinued from the study. Investigator decisions on dose changes (up or down) will only be permitted at study visits (or, due to AEs, at unscheduled visits for down-titration). Study medication will be given once daily in the evening, with or without food.

Based on the dosing information from the published literature and considering earlier and ongoing trials with memantine (sponsored by the pharmaceutical company Forest Laboratories, Berlin, Germany) in this age group, dosing was chosen weight-based, accordingly, also taking into account dose-unit availability in Europe (see Table 2).

### Production, packaging of the medication

All study medication will be identical in appearance and will be dispensed to patients or their parents by trained site personnel. A cooperation partner (H. Lundbeck A/S Pharmaceuticals, Copenhagen, Denmark) will provide the primary study material consisting of tablets containing 5 and 10 mg of memantine each and tablets containing placebo (in identical appearance). Study medication will be dispensed to the patient/parent at the investigator’s study site. Study medications will be packaged in blister packs or bottles. Clinical trial materials will be labelled according to the country’s regulatory requirements.

### Concomitant therapy

In general, concomitant medications with primarily central nervous system activity are not permitted in this study. A protocol attachment contains a list of medications and classes of medications that are or are not permitted during this study (depending and in accordance with the SPC for memantine, used in GOAT-1 and GOAT-2). Upon assent/consent by the patient and patient’s parent, the medications that are not allowed should be tapered off and stopped by visit 2, and be completely washed out by visit 3. Investigators should follow clinical guidelines with respect to duration of washout periods (minimum of five half-lives). Concomitant medication will be reported with compound, length of use, and doses in the clinical report form.

### Treatment compliance

Patient compliance with study medication will be assessed at each visit by direct questioning of parent and/or patient. Patients/parents will be asked to return both used (including empty) and unused blister cards distributed on the previous visit. Any deviation from the prescribed dosage regimen will be recorded. Final drug accountability reconciliation will be performed at the end of treatment or discontinuation.

During the double-blind treatment phase (study period II), a patient will be considered significantly noncompliant if he or she misses more than two consecutive days of study medication (full doses), or fails to take at least 80 % of prescribed doses of study medication (full doses) during two or more visit intervals. Similarly, a patient will be considered significantly noncompliant if he or she intentionally or repeatedly takes more than the prescribed amount of medication as judged by the investigator.

If a patient is noncompliant during an interval, the patient and parent will be counselled regarding the importance of compliance in this study.

### Statistical analysis

#### Clinical efficacy data

The end of the treatment phase will be taken as the primary endpoint. Change from BL in CY-BOCS total score will be used as the primary efficacy variable. As a secondary outcome measure a binary response score will be composed based on the change in CY-BOCS total score and the Clinical Global Impression-Improvement (CGI-I) scale at the end of the treatment phase (at least 30 % reduction in CY-BOCS total from BL and a score of 1 (very much improved) or 2 (much improved) in CGI-I scale). Additional symptom severity scores will be used as secondary efficacy measures.

General linear models will be applied on the CY-BOCS change score to compare the two treatment groups (active drug, placebo). Gender, age, investigational site and BL measurement will be included as covariates. Furthermore, diagnosis and diagnosis by treatment interaction will be entered in the model. A significant interaction effect will be followed up by separate analyses of the two diagnostic groups. In the presence of a high drop-out rate methods for missing data (e.g. last observation carried forwards (LOCF), mixed effect model repeat measurement (MMRM)) will be applied and sensitivity analyses will be performed to assess whether efficacy results are stable across different analysis methods. Logistic regression analyses will be performed to evaluate the effect of treatment on the binary response score. To study the impact of moderating factors on the outcome measures general linear models and logistic regression analyses will be applied, as appropriate. Gender, age, diagnostic group and investigational site will be included as covariates in all analyses. Multivariate statistical analysis of all data will be applied, reducing the chances of identifying false positives. This method can incorporate different types of predictors (clinical patient characteristics as well as neuropsychological and neuroimaging data, genetic and protein data). All analyses will be corrected for multiple testing as appropriate.

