### Aims and objectives

#### Primary objectives

To investigate: clinical effectiveness of the glutamatergic compound memantine in paediatric patients with OCD (GOAT-1) and ASD (GOAT-2) with respect to symptoms of ‘compulsivity’ (assessed as total score of the Children’s Yale-Brown Obsessive-Compulsive Scale (CY-BOCS; [52])) and to explore tolerability and safety (based on, e.g. laboratory measures, electrocardiography (ECG), adverse events) of the compound memantine in these clinical indications.

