Patients treated with glutamatergic compounds and their parents will have the benefit of potential medication effects on their symptomatology and the related burden of illness (reductions), plus of respective improvements in health-related quality of life. Equally important, all patients and parents can benefit from the high frequency and intensity of care – offered via the study visits by experienced child and adolescent psychiatry staff – that in general clearly extends beyond routine care settings.

An acute treatment period of as long as 12 weeks was chosen in order to increase the chance to reflect change/improvement based on medication treatment. With applying the respective adequate instruments, clinical outcome parameters will reflect compulsivity symptom clusters, but also comprehensive information on psychosocial functioning and health-related quality of life relevant in child and adolescent development. Contrasting findings across the patient populations will allow the assessment of disorder-related variation.

It is believed that the proposed project – with performing this pilot clinical trial in populations of children and adolescents with compulsivity disorders – will help to elucidate efficacy/effectiveness and tolerability/safety of glutamatergic medications, further to explore effects of moderating and mediating factors on the response to these compounds. Also, findings will allow assessment of medication effects on biomarkers and neural mechanisms underlying compulsivity. In addition, these pilot data will be made available to be used for potential future Paediatric Use Marketing Authorisation (PUMA) directed trial applications.

Respective MRI/MRS findings (from subgroups of patients, combined with the data from the TACTICS project’s COMPULS study) will help to clarify which mechanisms count for the compulsive behaviours in the considered disorders and subsequently to understand the links between compulsivity, impulsivity and addiction. These understandings will provide a basis for prospectively developing a guide for clinicians as to whether children are at high risk for negative outcome as severe compulsive behaviours and addictive behaviours in adolescence and adulthood.

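### Separate OCD and ASD results for CY-BOCS change are tied to a significant diagnosis-by-treatment interaction, a test with low power at 50 patients per disorder; report both disorder-specific estimates in every case

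*Protocol article*

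**What the plan says.** All references are to the protocol article.

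- **Primary objectives.** Effectiveness of memantine is to be investigated "in paediatric patients with OCD (GOAT-1) and ASD (GOAT-2) with respect to symptoms" of compulsivity. Each disorder carries its own sub-trial label.
- **Sample size calculation.** About 100 patients are planned, 50 per diagnostic subgroup. This number "will not allow for confirmatory statistical analyses but will be adequate for descriptive statistics", pilot-testing and hypothesis generation.
- **Randomisation.** Active drug and placebo are allocated 1:1.
- **Endpoints.** The endpoint for the effectiveness objective is baseline-to-endpoint change in CY-BOCS total score, in all patients.
- **Clinical efficacy data.** "Change from BL in CY-BOCS total score will be used as the primary efficacy variable". One general linear model compares the two treatment groups, with gender, age, site and baseline score as covariates, and with diagnosis and the diagnosis-by-treatment interaction as further terms. Then: "A significant interaction effect will be followed up by separate analyses of the two diagnostic groups". No other route to disorder-specific CY-BOCS results is given.
- **Discussion.** "Contrasting findings across the patient populations will allow the assessment of disorder-related variation".

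**The concern.** The article asks about two disorders and expects to contrast them, yet a significance test decides whether the separate analyses are carried out. That fits poorly with a sample declared unsuitable for confirmatory testing. The main product of a descriptive pilot is an estimate with an interval, and here that means one for each disorder.

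The test used as the condition is imprecise: with four equal cells, the standard error of the interaction is twice that of the pooled treatment effect. Two errors can follow. If memantine works in one disorder and not in the other, a non-significant interaction leaves a pooled figure that understates the benefit in one and suggests benefit in the other. If the interaction is significant, the observed difference has been selected for being large. Both matter for a study meant to generate hypotheses and whose data, according to the Discussion, may support later paediatric marketing-authorisation trials.

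**Working it through.** The article states no power, alpha, SD, effect size or dropout rate, so it has no figure of its own to reproduce. Everything below is in units of the SD of CY-BOCS change.

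**Inputs from the article:** 50 patients per disorder (Sample size calculation); 1:1 allocation (Randomisation).

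**Assumptions:** 25 patients per arm within each disorder (the article does not say that randomisation is stratified by disorder); two-sided alpha 0.05; a true difference between disorders of 0.3 to 0.8 SD; no dropout in the base case.

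**Standard errors**
- Treatment effect within one disorder: √(2/25) = 0.283 SD, so the 95% CI is ±1.96 × 0.283 = ±0.55 SD.
- Pooled treatment effect: √(2/50) = 0.20 SD, so ±0.39 SD.
- Interaction (difference between the two disorder effects): √(4/25) = 0.40 SD.

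**Difference needed for 80% power:** (1.96 + 0.84) × 0.40 = 1.12 SD.

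**Power of the interaction test**, Φ(d/0.40 − 1.96), with the noncentral t value (90 df) beside it:

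| True difference d | Normal | Noncentral t |
|---|---|---|
| 0.3 SD | 11.3% | 11.5% |
| 0.5 SD | 23.9% | 23.5% |
| 0.8 SD | 51.6% | 50.7% |
| 1.0 SD | 70.5% | 69.6% |
| 1.2 SD | 85.1% | 84.3% |

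**Sensitivity, for d = 0.5 to 0.8 SD (normal approximation)**
- 20% dropout (20 per cell, SE 0.447): 20% to 43%.
- Baseline adjustment with r = 0.5 (SE 0.40 × √0.75 = 0.346): 30% to 64%.
- Two-sided alpha 0.10: 35% to 64%.

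Power stays below 65% in every variant for differences up to 0.8 SD.

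**When the interaction is not significant.** Take effects of 0.8 SD in one disorder and 0 in the other. The interaction is non-significant in about 49% of trials (1 − 0.507). In a balanced design the pooled estimate is independent of the interaction estimate, so it averages (0.8 + 0)/2 = 0.40 SD in those trials: half the true effect in one disorder, and an apparent effect in the other where there is none.

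**When it is significant.** The estimated difference must exceed 1.96 × 0.40 = 0.784 SD in absolute size. Given that, its mean in the upper tail is d + 0.40 × φ(a)/[1 − Φ(a)], with a = (0.784 − d)/0.40.
- d = 0.8: a = −0.04, so 0.8 + 0.40 × 0.399/0.516 = 1.11 SD.
- d = 0.5: a = 0.71, so 0.5 + 0.40 × 0.310/0.239 = 1.02 SD (1.01 with the small opposite tail included).

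Differences that pass are thus overstated by about 0.3 SD and 0.5 SD on average.

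**The case against.** **The separate estimates already exist in the model.** A reader might infer that disorder-specific effects are estimated only after a significant interaction. The text does not say so. The word *only* is absent, diagnosis and its interaction with treatment are in the primary model in every case, and nothing says the interaction is dropped when non-significant. What is conditional is the separate follow-up analyses. This stands. Still, the article does not commit to reporting the model's disorder-specific contrasts, and the one rule it gives for showing results by disorder is conditional.

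**The primary question is answered by the pooled effect.** The endpoint is defined for all patients, the primary comparison is between the two treatment groups, and the Background presents compulsivity as a trait shared across disorders. So it would be wrong to say that the primary objective goes unanswered. This too stands. It does not remove the two-disorder wording of the objective or the contrast the Discussion expects.

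**The power figures are not the trial's own.** Correct: they rest on an assumed alpha, difference and cell size, and range from about 11% to 64% over the cases for 0.3 to 0.8 SD shown above. The conclusion holds across that range, though a difference of 1.2 SD would be detected with about 85% power.

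**Testing the interaction first is a common guard against multiple subgroup claims.** That is a good reason not to make disorder-specific significance claims, and a weak one for withholding estimates in a descriptive study.

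**Further inferences to avoid.** Nothing in the article says that a non-significant interaction will be taken to mean equal effects, and nothing shows that this test is the least powerful in the plan; the genetic and adverse-event analyses were not compared. Nor does unconditional reporting cure imprecision: power within one disorder is about 42% at 0.5 SD and 81% at 0.8 SD.

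**Conclusion.** The point holds as a should-fix. The rule ties the separate OCD and ASD analyses of CY-BOCS change to a test that, at 25 per cell and two-sided 0.05, has about 24% power for a 0.5 SD difference between disorders and 51% for 0.8 SD. It would often leave the pooled effect as the only result the article commits to when the disorders really differ, and it would overstate the differences that pass. These sizes depend on the assumptions listed in the working, none of which the article supplies. The primary model is sound and the study makes no confirmatory claim, so the fault lies in the reporting rule and not in the validity of the analysis.

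**What to change.** Replace the sentence on following up a significant interaction with:

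*The memantine-placebo difference with 95% CI will be reported for OCD and for ASD from the interaction model in every case, and the interaction will be reported as an estimate with 95% CI; its p-value will not decide whether disorder-specific results are shown.*

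Label the disorder-specific results exploratory, in line with the sample size section. No extra patients, data or model are needed, because the contrasts come from the model already planned. The cost is that the disorder-specific intervals will be visibly wide and will not settle the question in either disorder.
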